### Sample size determination

Sample size is calculated using a two-tailed test and indicated that to detect an absolute difference of 0.76% in HbA1c in favor of the intervention group with α = 0.05, β = 0.1 (90% power), and standard deviation of 1.0%, a sample size of 36 patients per group was required [18]. An additional 10% was added to allow for patients dropping out of the study, making a target sample size of at least 40 patients in each primary hospital, same as a previous study [19]. Our target enrolled patient number in each hospital is 100, and we plan to complete patient recruitment in 6 months. If the eligible patients have reached 100 in less than 6 months, we will continue the enrollment until the end of the sixth month. If the enrolled patients have not reached our target number at the end of the sixth month, we will continue to enroll patients for an extra month and then stop. We estimate that the final included patient number is around 80 to 120 in each primary hospital.

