#### Randomization and allocation concealment

The randomization protocol was used to select six out of 18 primary hospitals in Hunan province to carry out the study by using a standard protocol available in the website (http://stattrek.com/statistics/random-number-generator.aspx). There will be three centers in each group (intervention group and control group).

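### The 90% power claim comes from an independent-patient calculation that makes no allowance for allocating three whole hospitals to each arm, and its per-group figure reappears as a per-hospital figure

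*Protocol article*

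**What the plan says.** The Sample size determination section of the protocol article gives these inputs:
- The kind of test: "Sample size is calculated using a two-tailed test".
- The aim, which is "to detect an absolute difference of 0.76% in HbA1c in favor of the intervention group".
- The error rates chosen for that aim: "α = 0.05, β = 0.1 (90% power").
- The spread of HbA1c, for which it takes a "standard deviation of 1.0"%.

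From these it concludes that "a sample size of 36 patients per group was required". Losses are then covered by a 10% increase. The section gives the result as "making a target sample size of at least 40 patients in each primary hospital" and refers to an earlier study that used the same number. It then sets a target of 100 per hospital and expects 80 to 120. No ICC, design effect or number of hospitals enters the calculation.

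The Randomization and allocation concealment section describes the selection of six hospitals and then says: "There will be three centers in each group (intervention group and control group"). Other sections agree with allocation by hospital:
- The training section speaks of hospitals that have been assigned to the intervention group.
- The intervention section sets up three collaborative clinics.
- The Usual care clinics section excludes pharmacists from the control group.

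The Study design section differs: it says that eligible patients are randomly assigned to one group or the other.

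**The concern.** When whole hospitals are allocated, patients of one hospital tend to resemble each other, and the comparison rests on six units. The variance of the group difference then has a between-hospital part that more patients per hospital cannot reduce. A calculation for independent patients omits that part, so its 90% does not carry over to the design described. The protocol draws its hospitals from high-, medium- and low-income counties, so a near-zero ICC should not be assumed without saying so.

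The change of unit adds to the confusion. A number derived per group is presented as a number per hospital, so the reader cannot tell which design the power statement describes. The risk is that 90% is taken as a property of the trial, and that a null result is read more firmly than the design allows.

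**Working it through.** **Inputs from the Sample size determination and Randomization sections.** Difference d = 0.76, SD = 1.0, two-sided α = 0.05, power 90%, dropout 10%, minimum 40 and target 100 patients per hospital, 3 hospitals per arm.

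**Assumed, because the documents give no value.** ICC of 0.02, 0.05 and 0.10.

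**Step 1: reproduce the stated figure.** For independent patients, n per group = 2 × (1.960 + 1.282)² × 1.0² / 0.76² = 36.4. At 36 per group, power is 89.7% (normal) or 88.9% (t-test). The stated 36 is therefore sound to within rounding, as a result for independent patients.

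**Step 2: follow the unit.** 36 / 0.9 = 40. Both 36 and 40 are per group. The protocol attaches the 40 to each hospital, which makes 120 per arm.

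**Step 3: power with three hospitals per arm.** For m evaluable patients per hospital:
- Variance of a hospital mean: V = ICC + (1 − ICC)/m (SD = 1.0).
- Standard error of the difference: SE = √(2V/3).
- Power: noncentral t with 2 × (3 − 1) = 4 df, critical value 2.776, noncentrality 0.76/SE.

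Evaluable patients after 10% loss: 40 × 0.9 = 36 and 100 × 0.9 = 90.

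| Evaluable per hospital | ICC | V | SE | 0.76/SE | Power |
|---|---|---|---|---|---|
| 36 | 0.02 | 0.0472 | 0.177 | 4.28 | 89% |
| 36 | 0.05 | 0.0764 | 0.226 | 3.37 | 71% |
| 36 | 0.10 | 0.1250 | 0.289 | 2.63 | 52% |
| 90 | 0.02 | 0.0309 | 0.144 | 5.30 | 97% |
| 90 | 0.05 | 0.0606 | 0.201 | 3.78 | 80% |
| 90 | 0.10 | 0.1100 | 0.271 | 2.81 | 57% |

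**Step 4: the ICC that 90% power tolerates.** Solving for power = 90% gives an ICC of about 0.018 at 36 evaluable per hospital and about 0.034 at 90.

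**Step 5: detectable difference.** On 4 df, 90% power needs a noncentrality of 4.396. At 90 evaluable per hospital, 4.396 × SE gives 0.63, 0.88 and 1.19 HbA1c points at ICC 0.02, 0.05 and 0.10.

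**Step 6: limit from the number of hospitals.** With unlimited patients per hospital, V = ICC. Power is then 99.7%, 87% and 60% at the three ICC values.

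**Step 7: sensitivity to the reference distribution.** With a normal reference in place of t on 4 df, the tolerated ICC rises to about 0.056 (36 evaluable) and 0.072 (90 evaluable).

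**The case against.** Five points can fairly be made for the plan.

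1. The arithmetic is right, and if patients were randomised individually, as the Study design section says, the calculation would be adequate. Both parts stand. But the article describes no patient-level scheme, and its operational sections place whole hospitals in each arm.
2. The plan does not enrol 36 per group. A target of 100 per hospital is about 300 per arm and gives real protection: 97% power at ICC 0.02. This stands, although the protocol does not present the 100 as an allowance for clustering.
3. The change from group to hospital is not wholly unexplained, since an earlier study is cited, and it errs towards more patients. That is true, but a citation does not turn a per-group result into a per-hospital one.
4. The primary outcome is adjusted for its baseline value, and the protocol does not say whether the SD of 1.0 already reflects this. As an illustration, assume a baseline correlation of 0.5 at patient and hospital level, with 90 evaluable per hospital. Power at ICC 0.05 becomes about 90% on 4 df, or 82% if one df is spent on the covariate. At ICC 0.10 it becomes 68% or 59%. So the table above may be pessimistic.
5. The Data analyses section names t-tests, Mann–Whitney tests and a generalised linear mixed model, not a hospital-level t-test on 4 df. A normal reference is kinder (Step 7). With six allocated units, however, 4 df is the sounder basis.

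A reader might infer that the trial has only about even odds of detecting 0.76 points. The documents do not support that. It holds only near the top of the assumed ICC range, or at 12 patients per hospital (36 spread over three hospitals), which nobody plans.

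**Conclusion.** The point holds in limited form. The stated 90% power does not follow for the hospital-allocated design that most of the article describes, because the calculation treats patients as independent. It also does not follow that the trial is underpowered. At the planned size, 90% power is kept up to an ICC of about 0.034 and falls to about 80% at 0.05 and 57% at 0.10. At the stated minimum it is already slightly below 90% at ICC 0.02.

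These figures rest on an assumed ICC range, SD 1.0 without baseline adjustment, equal hospital sizes, 10% loss and a t reference on 4 df. The conclusion depends on allocation by hospital, which the Study design section contradicts.

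**What to change.** Rewrite the sample size paragraph:
- State the unit of allocation, and bring the Study design and Randomization sections into agreement.
- If hospitals are allocated, drop the step from 36 per group to 40 per hospital as the justification.
- Give power for 0.76 points, or the difference detectable with 90% power, for three hospitals per arm and about 90 evaluable patients each, over a stated ICC range. On the assumptions above these are 97/80/57% or 0.63/0.88/1.19 points at ICC 0.02/0.05/0.10.
- Say whether the SD of 1.0 is baseline-adjusted and which reference distribution is used. If either differs from the assumptions here, recompute the figures.

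No extra patients or hospitals are needed for this restatement. The cost is one rewritten paragraph and a less favourable stated power.

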### Covariates

The contents of the measures include four aspects, namely the socio-demographic parameters (age, gender, telephone, address, education, occupation and annual income), clinical parameters (Height, weight, waist to hip ratio, fasting blood glucose, 2-h postprandial blood glucose, HbA1c, diabetes complications, blood pressure and lipid files), process indicators (medication adherence, diabetes’ knowledge, lifestyle, diabetes treatment target and treatment behavior), and costs on diabetes.

### Dissemination

The research results will be disseminated through publications in peer-reviewed journals, academic conferences seminars and workshops. Articles and videos related to establishing physician-pharmacist collaborative diabetes clinics and diabetes management will be open to public in website for free.

## Discussion

It is urgent to establish feasible and cost-effective care mode to manage patients with diabetes in rural areas of China with the aim of ameliorating their glucose control, improving their medication adherence and lifestyle, and reducing the incidence of complications related to diabetes. There are two major reasons why people with T2DM in rural China have poor management. Firstly, physician density in rural areas is significantly lower than that in the urban areas. Due to lower income and limited professional development opportunities in the rural regions compared to the urban area, physicians in rural China are insufficient [20]. In 2013, physician densities at primary health centers and hospitals in rural areas were respectively 0.37 and 0.80 per 1,000 population, much lower than that in urban areas with 0.56 and 2.62 per 1,000 population [21–23]. Therefore, physicians in rural regions usually spend most of their time on disease diagnoses and treatment, while less time on patient education. Secondly, patients in rural China usually have lower socioeconomic status and education background, as a result, these patients are less aware of the importance of medication adherence, healthy lifestyle and regular monitoring of blood glucose levels [6]. Thus, patients in rural area often rush to the overloaded tertiary hospitals once they develop severe diabetic complications.

COVID-19 is the most infectious pandemic across the world in the past century, and the pandemic has placed unprecedented impact on health systems worldwide. Unfortunately, it is estimated that the pandemic may continue to exist for years. The Chinese government has taken several successful measures to prevent and control the pandemic, including aggressive containment strategy, hierarchical management, rational reallocation of resources and efficient contact tracing [24]. It is rational that many hospitals allocate a part of medical resources for COVID-19 prevention and control, resulting in reduced outpatient clinic capacities for chronic diseases care during the pandemic. However, it should be noted that insufficient glucose control will result in various acute and chronic complications, and the healthcare systems will have to cope with these after the COVID-19 pandemic. Moreover, diabetes has been proved as a susceptibility factor and independent predictor of worse prognosis in patients infected with SARS-CoV-2 [25, 26]. Therefore, it’s vital to improve diabetes management during the era of COVID-19 pandemic.

Studies have demonstrated that the pharmacist-physician collaborative care model are significantly helpful to improve the outcomes of patients with diabetes. A study consisting of 2,480 patients with diabetes included in both the collaborative care group and the usual care group from 6 hospitals and 22 patient-centered medical home practices showed that the pharmacist-physician collaborative care mode remarkably improved HbA1c, blood pressure and lipid files, as well as reduced hospitalizations compared to usual care, yielding an estimated cost savings of up to $2,619 per patient [27]. By providing the services of diabetes education and disease management via providing information and feedback to patients and recommendations to providers in the collaborative care practice, pharmacists helped more patients reached the goal of HbA1c below 7% [28]. Moreover, a systematic review consisting of 25 studies demonstrated that pharmacist-managed services in people with diabetes could save costs from $7 to $65,000 per person per year, and generated higher quality-adjusted life years [12]. Therefore, we should notice that in the era of COVID-19 pandemic, when part of physicians and nurses are taking responsibilities of preventing and controlling the pandemic, well trained pharmacists are valuable medical resources for diabetes management. The pharmacist-physician collaborative clinic may be a promising care model for patients with diabetes in China. Yet, to our knowledge, no study has ever investigated if this model could be adapted in primary hospitals of China. This proposed study will be the first to implement the pharmacist-physician collaborative clinic model to manage patients with T2DM in primary hospitals, and to evaluate the efficacy and cost-effectiveness of this program through a multi-site randomized controlled trial in Human province with 66.44 million residents. If effective, the physician-pharmacist collaborative clinics can be adapted and used in primary hospitals across China to improve glycemic control, enhance medication adherence, decrease incidence of complications and reduce patients’ dependence on physicians. Findings from the present study are meaningful for developing evidence-based diabetes care policy in rural China, especially in the COVID-19 pandemic era.

This proposed study has some limitations. Firstly, we will only carry out the study in Hunan province, where the economic level is at the upper middle level in China. The limited geographical reach of the proposed study may influence its generalizability. Secondly, we plan to follow up enrolled patients for only 12 months, the long-term effects of the physician-pharmacist collaborative clinics on the outcomes may be not known. We will follow up the patients if they prefer to continue staying in the collaborative clinics after one year intervention.

In summary, we will establish and evaluate the impacts of the physician-pharmacist collaborative clinics on diabetes management in primary hospitals of Hunan province in China. This project will be a great pilot to explore and show pharmacists’ new value in health care, and is expected to make a significant contribution to the development of a new evidence-based health policy for diabetes management, particularly for rural residents in China during and after the COVID-19 pandemic.

### Trial status

Recruitment has begun in May 2021.

## Data Availability

The datasets generated and/or analyzed during the current study are not publicly available but are available from the corresponding author on reasonable request.

## Abbreviations

T2DM: Type 2 diabetes mellitus
COVID-19: Coronavirus Disease 2019
WHO: World Health Organization
IDF: International Diabetes Federation
MTM: Medication therapy management
AE: Adverse event
PI: Principal Investigator
CRF: Case Report Form
FBS: Fasting blood glucose
2hPBG: 2-Hour postprandial blood glucose
SPSS: Statistical Package for the Social Sciences
QALYs: Quality-adjusted life-years
ICER: Incremental cost effectiveness ratio
